# Efficacy of donepezil for the treatment of oxaliplatin-induced peripheral neuropathy: DONEPEZOX, a protocol of a proof of concept, randomised, triple-blinded and multicentre trial

**DOI:** 10.1186/s12885-022-09806-8

**Published:** 2022-07-07

**Keywords:** Pain, Chemotherapy-induced peripheral neuropathy, Anticholinesterase, Donepezil, Oxaliplatin, Study protocol

## Abstract

**Background:**

The use of oxaliplatin in digestive tract cancers could induce severe peripheral neuropathy (OIPN) decreasing the quality of life of patients and survivors. There is currently, no univocal treatment for these peripheral neuropathies. Donepezil, a reversible inhibitor of cholinesterase, used to treat Alzheimer’s disease and dementia, is reported to have a good safety profile in humans, and preclinical data have provided initial evidence of its effectiveness in diminishing neuropathic symptoms and related comorbidities in OIPN animal models.

**Methods:**

The DONEPEZOX trial will be a proof-of-concept, randomised, triple-blinded, and multicentre study. It will be the first clinical trial evaluating the efficacy and safety of donepezil for the management of OIPN. Adult cancer survivors with OIPN that report sensory neuropathy according to QLQ-CIPN20 sensory score (equivalence of a grade ≥ 2), at least 6 months after the end of an oxaliplatin-based chemotherapy will be included. Eighty patients will be randomly assigned to receive either donepezil or placebo over 16 weeks of treatment. The primary endpoint will be the rate of responders (neuropathic grade decreases according to the QLQ-CIPN20 sensory score) in the donepezil arm. The severity of OIPN will be assessed by the QLQ-CIPN20 sensory scale before and after 16 weeks of treatment. The comparison versus the placebo arm will be a secondary objective. The other secondary endpoints will be tolerance to donepezil, the severity and features of OIPN in each arm before and after treatment, related-comorbidities and quality of life. Fleming’s one-stage design will be used for sample size estimation. This design yields a type I error rate of 0.0417 and power of 91% for a responder rate of at least 30% in donepezil arm. A total of 80 randomized patients is planned.

**Discussion:**

This study will allow, in the case of positive results, to initiate a phase 3 randomized and placebo-controlled (primary endpoint) clinical study to assess the therapeutic interest of donepezil to treat OIPN.

**Trial registration:**

NCT05254639, clincialtrials.gov, Registered 24 February 2022.

## Background

Chemotherapy-induced peripheral neuropathy (CIPN) is a common adverse effect of neurotoxic anticancer drugs (platinum salts, taxanes, vinca alkaloids, bortezomib, thalidomide), which impacts the patients’ quality of life [1]. CIPN occurs in approximately 68% of patients treated with multiple agents [2]. The incidence depends on the chemotherapy regimen, the duration of exposure, and assessment methods [1, 3]. CIPN is the consequence of damage to the peripheral nervous system caused by neurotoxic anticancer agents. These CIPN are mainly characterized by symmetrical sensory disorders with a distal predominance and without truncal or radicular systematization. Most of the symptoms of CIPN correspond to a clinical picture of sensory polyneuropathy, causing loss of sensitivity, paresthesia, dysesthesia, burning sensations, altered fine motor skills and neuropathic pain. About 30% of patients with sensory CIPN also suffer from neuropathic pain [4, 5]. Motor symptoms such as cramping, twitching, muscle atrophy and vegetative disorders can also occur [1]. With cumulative doses, symptoms progress from the ends of the hands and feet to the wrists and ankles and finally the arms and legs [6]. In addition, the perioral or face region, and auditory system can also be affected [7–9].

Oxaliplatin is widely used to treat digestive tract cancers despite being extremely neurotoxic. This neurotoxicity is often dose-limiting and hampers the efficacy of chemotherapy [10]. Oxaliplatin-induced peripheral neuropathy (OIPN) may occur either shortly after oxaliplatin infusion (up to 90% of patients) [2] characterized mainly by acute and transient cold hyperalgesia, or as late-onset chronic cumulative peripheral neuropathy (30–50% of patients) [11]. The resulting neuropathy symptoms can be persistent and definitive (> 24 months [11] and > 48 months [12, 13]), and associated with psychological distress (anxiety and depression) and a decrease of patients’ health-related quality of life (HRQoL) [14].

Although a number of compounds have been investigated to prevent or treat CIPN, none of them are sufficiently effective to be used routinely in clinical practice [15, 16]. Only duloxetine was recommended by ASCO and ESMO for neuropathic pain-related to CIPN [15, 16]. As a result of the lack of clear evidence, the current strategies used to reduce CIPN essentially consist in modifying of the chemotherapy doses and infusion schemes, although sometimes it continues to worsen despite stopping oxaliplatin. This aggravation can be linked to risk factors such as diabetes and excessive alcohol consumption. Little or no follow-up or treatment is offered to patients developing chronic neuropathy after their chemotherapy [10, 13, 17]. This leads to medical wandering, which is very harmful for the patient. Lastly, OIPN is one reason why, despite negative results of the IDEA trial [18], oxaliplatin-based adjuvant treatment of high-risk stage II and low-risk stage III colon cancers is now used for only 3 months as standard of care as compared the previously 6 months of adjuvant treatment.

Donepezil, a reversible inhibitor of cholinesterase, is used to treat Alzheimer’s disease and dementia [19]. Donepezil is reported to have a good safety profile in humans [20–22]. In addition, preclinical data have provided initial evidence of its effectiveness in diminishing neuropathic symptoms and related comorbidities in OIPN animal models [23, 24]. The preclinical evidence and the lack of clinical trial data led us to design the first proof of concept study to assess the efficacy and tolerance of donepezil in the treatment of OIPN in cancer survivors.

### Preclinical & clinical arguments for using donepezil to treat OIPN

Preclinical works have demonstrated that donepezil was able to prevent and treat tactile allodynia in oxaliplatin-treated animals [23, 24]. More precisely, OIPN was responsible of an increase of the cholinergic neurotransmission involving acetylcholine muscarinic M2 receptors (m2AChRs) in the insular cortex of oxaliplatin-treated rats. In the insular cortex, choline (acetylcholine metabolite) concentration was significantly increased and correlated to mechanical allodynia. Moreover, m2AChRs were also up-regulated, and insular micro-injection of oxotremorine (m2AChRs agonist) suppressed mechanical allodynia. Finally, the antineuropathic effect of donepezil was blocked by insular micro-injection of methoctramine (m2AChRs antagonist) [24]. Interestingly, data have highlighted the beneficial effect of donepezil on neuropathic symptoms in different neuropathic pain conditions, likely found in patients affected by CIPN, without significant adverse effects. Likewise, several studies demonstrated that donepezil induces analgesic and neuroprotective effects [25–29]. Recently, a preclinical study demonstrated that donepezil induced an antineuropathic effect in diabetic mice with neuropathic pain [30].

Clinical studies have confirmed the potential antineuropathic effect of donepezil. Boyle et al*.* [31] showed in healthy volunteers that donepezil (associated with gabapentin) reduced the pain thresholds (better than gabapentin alone) caused by the stimulation of the sural nerve without severe adverse effects. Similarly, this result was also observed in two studies with patients suffering from various neuropathic pain [32, 33]. Finally, a case report demonstrated an analgesic effect of donepezil in a patient with painful Alzheimer’s disease [34]. Moreover, donepezil improved depression and anxiety scores and HRQoL in cancer patients treated by opioids [35].

All of these clinical and preclinical data have thus highlighted the potential beneficial effect of donepezil on neuropathic symptoms, without any severe adverse effect. We therefore hypothesized that the use of donepezil could reduce the symptoms of OIPN and limit the decrease in HRQoL and reduce psychological distress (anxiety and depression) in digestive cancer survivors.

### Mechanism of CIPN

Better knowledge of the neurotoxicity mechanism induced by anticancer agents is now available. Peripheral neuropathy can result from various causes: damage of the microtubule transport of axons; distal axonal degeneration [36]; morphological change of the nuclei of dorsal root ganglia (DRG) neurons; alteration of mitochondrial function in axons; and intra-axonal accumulation of sodium and calcium by disruption of voltage-gated sodium (Nav) and potassium channels [37]. Nerve damage depends on the anticancer drug administered. Oxaliplatin is known to damage the nuclei of DRG neurons; cause channelopathies of the Nav channel (variation of expression and functionality) and cold receptors of the transient receptor potential family (TRPM8 and TRPA1) [38]. An increase in the glutamate level in the spinal dorsal horn has also been observed in oxaliplatin-treated animals [39], suggesting an involvement of glutamatergic neurotransmission in pain hypersensitivity development induced by oxaliplatin. The chronic sensory form is considered to be induced by morphological and functional changes in the DRG, resulting from the local deposition and accumulation of oxaliplatin. Mitochondrial toxicity could represent an important pathophysiological basis for the chronic neurotoxicity of platinum derivatives [40], as well as satellite glial cell activation in DRG [41].

### Current treatment available for CIPN

Several therapeutic agents (antioxidants, neuroprotective agents, analgesics, anticonvulsants, antidepressants, dietary supplements, etc.) have been found promising for CIPN treatment [42]. However, the evidence of their effectiveness remains controversial and the treatment of CIPN is still largely symptomatic. Antidepressants, antiepileptics and current analgesics are the only options available to clinicians, mainly for treating neuropathic pain symptom; however, their effectiveness is limited and associated with significant adverse events like drowsiness. Two studies demonstrated the potential interest of duloxetine for managing CIPN [43, 44], but these studies assessed only the neuropathic pain component (which represents about 30% of patients with CIPN [4, 5]), or they were not randomized or controlled. Lastly, a recent study has shown the preventive effect of Renin-Angiotensin System Inhibitors but this must be confirmed in a randomized controlled trial [45]. The recent update of ASCO and ESMO guidelines for the prevention and treatment of CIPN states that no treatment can be recommended for the prevention of CIPN and only duloxetine can be recommended (level: moderate) for the treatment of neuropathic pain related to CIPN [15, 16]. Therefore, to avoid severe CIPN, dose reduction or discontinuation of the neurotoxic anticancer drug is the only option to limit the progression of CIPN [46, 47].

Donepezil, marketed for the treatment of Alzheimer’s disease [48], is known to be neuroprotective [49, 50], anxiolytic and antidepressant [51], with a known safety profile based on Alzheimer patients, and may thus be a suitable candidate for treatment of CIPN.

## Methods / design

### Study design

The present study is a randomised, triple-blinded (patients, clinicians and pharmacists), and multicentre proof-of-concept trial that assesses the efficacy and safety of donepezil in patients with OIPN. The plan is to include 80 patients from 26 cancer centres and hospitals in France. The duration of the study is 20 weeks for the patients, including 4 weeks for treatment initiation, 12 weeks of stable treatment and 4 weeks of follow-up.

### Study objectives

The primary objective is to assess the curative efficacy of donepezil on the severity of OIPN in patients having received and completed oxaliplatin-based chemotherapy indicated for colorectal and pancreatic cancers and eliciting QLQ-CIPN20 sensory score ≥ 30 / 100 (equivalent to grade ≥ 2 peripheral neuropathy). Efficacy will be based on the percentage of responders (decrease of peripheral neuropathic grade according to the QLQ-CIPN20 sensory score) only in the donepezil arm (see the “Study endpoints” chapter for details).

The secondary objectives are safety (type, intensity, frequency of adverse effects and treatment discontinuation rate due to adverse effects) of donepezil, and its efficacy compared to the placebo arm, for:Neuropathic symptoms throughout the study (severity and responders),Anxiety and depression,OIPN grade,Neuropathic pain,Health-related quality of life,Patient global impression of change (PGIC),Consumption of painkillers.

### Inclusion and exclusion criteria

Participants will be adult cancer survivors with OIPN diagnosed for more than 3 months and not relieved by the usual treatments.

#### Inclusion criteria

◦ Adult Male / Female who received oxaliplatine-based chemotherapy for colorectal or pancreatic cancers,◦ QLQ-CIPN20 sensory score ≥ 30 / 100 (equivalent to the National Cancer Institute—Common terminology criteria for adverse events (NCI-CTCAE) v4.0 grade of neuropathy ≥ 2),◦ Diagnosis of OIPN treated or not by stable antineuropathic treatment (opioids, pregabalin, gabapentin, duloxetine and other antidepressants or anticonvulsants) for at least 1 month,◦ Chemotherapy completed for at least 6 months,◦ Patients affiliated with the French national health insurance,◦ Written informed consent,◦ French language comprehension.

#### Exclusion criteria

◦ Ongoing cancer,◦ Pregnancy or breastfeeding (required contraception),◦ Patient with chronic progressive disease inducing pain (excluding OIPN),◦ Diabetic patient (excluding non-insulin-treated or insulin-treated diabetes of less than 5 years) or presence of a proven diabetic neuropathy◦ Other types of neuropathies,◦ ALT / AST more than 3 times the normal value,◦ Severe cardiovascular disease, bradycardia (< 55 bpm), heart conduction disorders,◦ History or active gastroduodenal ulcer,◦ Asthma or obstructive pulmonary disease,◦ Allergy to donepezil or piperidine derivatives,◦ Drug interactions: CYP3A4 inhibitors (ketoconazole, itraconazole and erythromycin); CYP2D6 inhibitors (quinidine, fluoxetine) and enzymatic inducers (rifampicin, phenytoin, carbamazepine),◦ Dependence on alcohol and/or drugs,◦ Psychotic disorders, patient under antipsychotics.

No therapeutic change will be generated by the protocol; patients will be treated with donepezil or placebo in addition to their current treatment of OIPN, if any. However, no therapeutic change for OIPN or pain will be allowed throughout the study.

Patients can discontinue the study treatment for any of the following reasons: intolerance to donepezil and significant adverse events; and can be withdrawn from analysis for any of the following reasons: modification of the antineuropathic / analgesic therapy (if any) during the study, withdrawal of consent and serious protocol deviation.

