#### Secondary endpoints

The evolution of all the secondary parameters will be studied in an intragroup (before *vs.* after treatment) and an intergroup (placebo *vs.* donepezil arm): i) Sensory, motor and autonomic scales from the QLQ-CIPN20 questionnaire (see below); ii) Grading of OIPN by NCI-CTCAE v4.0: this scale will be used to grade the severity of sensory neuropathy from 1 to 4 (1 = Asymptomatic, 2 = Moderate symptoms; limiting instrumental of Activities of Daily Living [ADL], 3 = Severe symptoms; limiting self-care ADL, 4 = Life-threatening consequences; urgent intervention indicated); iii) Assessment of neuropathic pain: monthly assessment of pain felt in the last week by 11-point NRS. This scale is used for adults and children 10 years old or older patient self-reporting of pain (score of 0 = no pain and 10 = worst possible pain). If NRS ≥ 4/10, neuropathic pain will be validated by the DN4 interview questionnaire (“*Douleur Neuropathique 4*”) will be mandatory. The interview portion of the DN4 questionnaire is a clinician-administered screening tool for neuropathic pain [59]. The questionnaire includes 7 items (YES or NO, the test is positive for a score ≥ 3/7). If the patient have a positive DN4 and a pain intensity ≥ 4/10 (NRS), neuropathic pain will be confirmed and will be characterized by the Neuropathic Pain Symptom Inventory (NPSI) questionnaire. This self-reported questionnaire assesses neuropathic pain symptoms [60], and includes 12 items; iv) HRQoL by the QLQ-C30 questionnaire (EORTC): this auto-questionnaire (EORTC) assesses the HRQoL of cancer patients, and includes five functional scales, three symptom scales, an overall HRQoL scale, and a number of additional elements assessing other symptoms; v) Anxiety and depression by the hospital anxiety and depression scale (HADS) questionnaire: this auto-questionnaire detects anxiety and depressive disorders, and includes 14 items rated from 0 to 3 (7 questions for anxiety and 7 for depression). The following interpretation is proposed for each of the two total scores: ≤ 7: absence of symptomatology; 8 to 10: suggestive symptomatology; ≥ 11: indicative symptomatology; vi) Patients’ Global Impression of Change (PGIC): PGIC [61] assesses the general effectiveness of the treatment according to the impression of patient, with the scores from 1 to 7 (from aggravated to very improve); vii) Safety: the time to treatment failure will be assess. This is the interval between randomization to treatment discontinuation for any reason. The assessment of adverse events (AEs) associated with study treatment will be also assessed by NCI-CTCAE v4.0. Any AEs will be collected daily by the patient and during the monthly visits. AEs will be categorized according to their intensity, treatment-related or not and by type. At last, viii) Assessment of painkiller consumption (if any): drug consumption for OIPN will be assessed throughout the study.

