#### Visits after 4, 8 and 12 weeks of initiation treatment (V1, V2 and V3)

The following will be performed:The patient will return the empty or unused study treatment from the last treatment period,Completion of QLQ-CIPN20 questionnaire and 11-point NRS pain,Assessment of painkiller consumption (if applicable),Electrocardiogram and heart rate,Blood sampling (hepatic function, complete blood count),Body weight,Assessment of safety (adverse effects by NCI CTCAE v4.0),Determination of the dose to be delivered according to the treatment efficacy and tolerance, for the 4-weeks period. In the case of efficacy or poor tolerance, the dose will remain at 5 mg/day. If the study treatment is well tolerated but does not show efficacy (according to QLQ-CIPN20 score), the dosage will be increased to 10 mg/day.

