#### Statistical analysis

All statistical analyses will be performed using SAS software version 9.4 before breaking the randomization codes, according to International Conference on Harmonization-Good Clinical Practice guidelines. A two-sided *p*-value of less than 0.05 will be considered for the statistical significance of all the analyses. The results will be expressed as hazard-ratios and 95% confidence intervals. Secondary analyses will be exploratory.

The baseline description of the patients included in the analysis will be carried out, without presenting inferential statistical tests (according to recommendations). As part of a proof-of-concept, only patients who have completed the study (treatment received in its entirety for 16 weeks whatever the dose = per protocol population) will be analyzed for the primary endpoint. The primary endpoint will be the rate of responders and will be described using frequency and percentage. A 95% one-sided confidence interval will also be calculated. Subgroup analyses for the primary endpoint will be planned for each stratum of the randomization (neuropathy grade, age of neuropathy and type of chemotherapy).

For the secondary endpoints, analyses will be performed on the intention-to-treat and per-protocol populations and compared to the placebo arm.

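### Patients who change pain therapy can be withdrawn from analysis, with no limit to the per-protocol set; this conflicts with the planned ITT analyses and, for painkiller consumption, selects on the outcome

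*Protocol article*

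**What the plan says.** The Study objectives section of the protocol article lists "Consumption of painkillers" among the outcomes on which donepezil's efficacy is compared with placebo. The Secondary endpoints section makes it item viii: "drug consumption for OIPN will be assessed throughout the study". It also announces that "The evolution of all the secondary parameters will be studied in an intragroup" manner and between arms.

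Two rules in the Exclusion criteria section bear on that endpoint. The first is a ban: "However, no therapeutic change for OIPN or pain will be allowed throughout the study". The second concerns patients who break it. They "can be withdrawn from analysis for any of the following reasons: modification of the antineuropathic / analgesic therapy (if any) during the study". The wording is permissive, gives no criterion, covers increases and decreases alike, and names no analysis set.

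The Statistical analysis section states: "For the secondary endpoints, analyses will be performed on the intention-to-treat and per-protocol populations and compared to the placebo arm". It defines the per-protocol set in one way only: "treatment received in its entirety for 16 weeks whatever the dose = per protocol population". Modification of therapy is not part of that definition. The section also declares the secondary analyses exploratory.

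**The concern.** Two stated rules give different answers for the same patient. Someone who changes an analgesic and takes study treatment for the full 16 weeks belongs to the ITT set and to the per-protocol set under Statistical analysis, yet may be dropped under Exclusion criteria. Followed literally, the second rule can remove randomised patients even from the ITT comparison.

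For most endpoints this is an ordinary post-randomisation exclusion. For painkiller consumption it is worse, because changing therapy is the outcome being measured, so removal depends directly on its value. The ban adds a separate problem of interpretation: it suppresses much of the variation that the endpoint is meant to detect, and no analysis set can restore it.

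The mismatch also reaches the primary analysis, which is run in the per-protocol set. Whether a completer who changed an analgesic counts there is not settled.

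**Working it through.** **The plan's own figure.** The article states no rate for painkiller consumption. The only design figures are for the primary rule (Sample size estimation): at least 7 responders in 33, with null rate 10% and alternative 30%. Exact binomial tails give P(X ≥ 7 | 33, 0.10) = 0.0417 and P(X ≥ 7 | 33, 0.30) = 0.906. Both stated values (0.0417 and 91%) reproduce, and this point does not alter them.

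**The two sections side by side, for a completer who changes an analgesic.**

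| Source | ITT (secondary endpoints) | Per protocol (primary and secondary) |
|---|---|---|
| Statistical analysis | in | in (16 weeks completed) |
| Exclusion criteria | removable | removable |

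**Effect of removal on painkiller consumption.** Score each patient −1 (reduced), 0 (unchanged) or +1 (increased). Let r and i be the shares reducing and increasing in an arm, and let wr and wi be the shares of reducers and increasers removed, with the same rule in both arms. The observed arm mean is

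[i(1 − wi) − r(1 − wr)] / [i(1 − wi) + r(1 − wr) + (1 − r − i)].

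The effect is donepezil minus placebo; negative favours donepezil.

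- *All changers removed (wr = wi = 1).* Every remaining patient scores 0, so the difference is 0 whatever the true rates. This needs no assumption about rates.
- *Assumed rates, first case:* donepezil r = 25%, i = 10%; placebo r = 10%, i = 10%.
  - True: (0.10 − 0.25) − (0.10 − 0.10) = −0.150.
  - Only increasers removed: −0.25/0.90 − (−0.10/0.90) = −0.278 + 0.111 = −0.167 (exaggerated).
  - Only reducers removed: 0.10/0.75 − 0.10/0.90 = 0.133 − 0.111 = +0.022 (sign reversed, close to nil).
- *Assumed rates, second case:* donepezil r = 10%, i = 5%; placebo r = 10%, i = 25%.
  - True: (0.05 − 0.10) − (0.25 − 0.10) = −0.200.
  - Only increasers removed: −0.10/0.95 − (−0.10/0.75) = −0.105 + 0.133 = +0.028.
  - Only reducers removed: 0.05/0.90 − 0.25/0.90 = −0.222.

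None of these distortions requires anyone to know the treatment arm.

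**Effect of the ban.** Suppose 30% on donepezil and 10% on placebo would reduce painkillers if free to do so (assumed). If a common share s of these changes is suppressed, the observed difference is (1 − s) × 20 points: 10 points at s = 0.5, 4 at s = 0.8 and 0 at s = 1. With 40 per arm, approximate power is 61% with no suppression, 32% at s = 0.5 and 15% at s = 0.8. ITT analysis does not recover what the ban has suppressed.

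**The case against.** **Blinding.** A reader might infer that discretionary removal could produce almost any result. With p the share who change and w the share of changers removed in an arm, the observed share is p(1 − w)/(1 − pw). For assumed p of 30% on donepezil and 10% on placebo, removing only placebo changers gives 12/40 against 0/36, or +30 points; removing only donepezil changers gives 0/28 against 4/40, or −10. With 20% changing in each arm and no true effect, the range is −20 to +20. The documents do not support reading these as realistic risks. The Study design section blinds patients, clinicians and pharmacists, and Statistical analysis places the analyses before the codes are broken. If removal is blind and the arms change therapy equally, the expected difference stays 0. The figures also pool increases with decreases, so they are mathematical bounds with no direct efficacy meaning. Blinding is not perfect: the primary endpoint section lets the investigator request unblinding after benefit at end of treatment, and side effects may unmask some patients. What blinding does not prevent is the distortion of a true effect by an even-handed rule.

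**ITT is already planned.** True, and withdrawal from analysis, listed next to serious protocol deviation, can be read as exclusion from the per-protocol set alone. The text does not say so, and the per-protocol definition does not mention therapy changes. This is a conflict between two stated rules, not a detail left to an analysis plan.

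**Fixed background therapy is ordinary design.** This stands. It protects the QLQ-CIPN20 and pain endpoints. A reader might infer that it makes the consumption endpoint worthless; that goes too far, because as-needed intake within a stable prescription can still vary.

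**The missing-data analyses.** The worst-case scenario covers patients with missing data. A changer whose consumption was recorded is not missing, so it does not clearly repair the selection.

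**Conclusion.** The point holds as a conflict between the Exclusion criteria and Statistical analysis sections, with a particular consequence for painkiller consumption. Removal of all changers forces that comparison to zero; removal in one direction can exaggerate or reverse it. The zero is certain. The other sizes rest on assumed rates, because the article gives no rate of painkiller use or change. The rates may be generous: Inclusion criteria admit patients without antineuropathic treatment, and those with no painkillers at baseline cannot reduce them.

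The impact is minor. The affected between-arm analyses are exploratory. A reader might infer that the primary result is compromised; the documents do not support that. The 7-in-33 threshold and its error rates are unchanged, and what remains open is only which completers are counted. The ban itself calls for cautious reading of a null consumption result, not for a different design.

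**What to change.** In Exclusion criteria, state that modification of antineuropathic or analgesic therapy never removes a patient from the ITT analyses of the secondary endpoints and can affect only the per-protocol set. Replace the discretion with a fixed rule, applied before unblinding, and write the same rule into the per-protocol definition in Statistical analysis. That also settles who enters the primary count.

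Analyse painkiller consumption in all randomised patients by direction of change from V0 (decrease, none, increase). State in advance that, because of the ban, a null result will not be read as absence of effect. Whether concomitant pain treatment stays fixed is a clinical matter for the sponsor.

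The cost is a few sentences. Consumption is already recorded at V0, at V1 to V3, at V4 and at the follow-up call, so no new data are needed. The downside is that the ITT analyses will include patients who departed from the stable-treatment rule, and that an exclusion now left to judgement becomes fixed.
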